### Study outcomes

#### Primary outcome

The primary outcome is the occurrence of PE. PE will be defined according to the American College of Obstetricians and Gynecologists 2013 recommendation [19]. The systolic blood pressure should be 140 mmHg or more, and/or the diastolic blood pressure should be 90 mmHg or more on at least two occasions 4 h apart, developing after 20 weeks of gestation in previously normotensive women (blood pressure < 140/90 mmHg). There should be proteinuria of 300 mg or more in 24 h, a urinary/protein creatinine ratio of at least 0.3 mg/dl or two readings of at least 2+ on dipstick analysis of midstream or catheter urine specimens if no 24-h collection is available. Efficacy will be assessed by the development of PE at any gestation after 20 weeks of pregnancy as defined above.

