### Randomization

Randomization will be performed using a web-based computerized central randomization system, the Interactive Web Response System (http://bjdx.clinicalcloud.com.cn/Login.aspx), in a 1:1 allocation ratio. The website randomly assigns a randomization code to each participant. Eligible women will be randomized to one of the two groups. Knowledge of the treatment allocation is open to the investigators and the participants.

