### Intervention and control groups

Women will be assigned into one of two groups. The control group will receive standard antenatal care for high-risk women, whereas the intervention group will receive standard antenatal care for high-risk women plus aspirin prophylactic treatment. LDA (100 mg/d, enteric-coated aspirin tablets; Bayer Corporation, Leverkusen, Germany) should be taken nightly from the recruitment time (at 12–20 weeks of gestation) and stopped at 34 weeks of gestation or in the event of early delivery. This is an open-label RCT, and all of the participants, clinicians and investigators will be aware of the study group assignment.

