### Data collection and analysis

#### Data collection

Data will mainly be collected prospectively in three rounds of surveys and from medical records. The baseline survey will be administered by a health worker at a local hospital in the first antenatal visit after obtaining written informed consent from women who have agreed to participate in the study. The follow-up surveys will be conducted at the hospital after within 2 days of delivery by a healthcare worker. The final survey will be a phone interview at day 42 after delivery. In addition, clinical data will be collected from the local hospital.

Participant data will be collected from a paper case report form (CRF) and then entered into an electronic case report form (eCRF) (http://bjdx.clinicalcloud.com.cn/Login.aspx) for further data sorting. Data on pregnancy and neonatal outcomes will be collected from the hospital maternity records or the general medical practitioners.

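### In a fully open-label trial, the primary outcome rests on repeat blood pressures and on whichever urine test was collected, so unequal work-up or classification could create or hide a difference in pre-eclampsia

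*Protocol article*

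**What the plan says.** The Protocol article states the lack of masking twice. Under Randomization: "Knowledge of the treatment allocation is open to the investigators and the participants". Under Intervention and control groups: "This is an open-label RCT, and all of the participants, clinicians and investigators will be aware of the study group assignment".

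Under Primary outcome: "The primary outcome is the occurrence of PE". The definition has two parts. Raised pressure must be found on two occasions four hours apart, after 20 weeks. Proteinuria must also be shown, by one of three routes:

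- "There should be proteinuria of 300 mg or more in 24 h";
- "a urinary/protein creatinine ratio of at least 0.3 mg/dl";
- "two readings of at least 2+ on dipstick analysis of midstream or catheter urine specimens if no 24-h collection is available".

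On the source of the data, the Data collection section says: "Data on pregnancy and neonatal outcomes will be collected from the hospital maternity records or the general medical practitioners". Survey rounds, paper case report forms and an eCRF are described alongside this.

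The Specimen collection section withholds some results from the managing clinicians. That concerns the stored samples and biomarkers; nothing similar is said of blood pressure or urine protein.

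**The concern.** Open-label treatment is a defensible design. It matters more when the primary outcome is not a hard event but a diagnosis assembled from measurements. Here a woman becomes a case only if her pressure is rechecked and her urine is tested, and the third urine route applies or not according to what was collected. The people around her, and the woman herself, know whether she takes aspirin.

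If awareness of allocation changes how readily women are rechecked, how their urine is quantified, or how borderline results are turned into a case, the two arms no longer have the same chance of having a true case counted. The trial could then report a benefit that is only a difference in detection, or miss a real one. Preterm PE and severe PE, both key secondary outcomes in Table 1, start from the same diagnosis and inherit the problem.

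**Working it through.** **Step 1. How testing changes case status.** The article gives no figure for ascertainment, so there is none to reproduce. The mechanism follows from the definition.

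- Take two women with the same qualifying pressures, the same two 2+ dipsticks and no protein/creatinine ratio. One has a 24-h collection that returns below 300 mg; the other has none. Under the printed definition the first is not a case and the second is. Here *more* testing *removes* a case.
- Take two women with one raised pressure and true disease. One is rechecked and has her urine tested; the other is not. Only the first can be counted. Here *more* testing *adds* a case.

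So heavier work-up of one arm can move its PE rate either way. The direction of any bias cannot be read from the documents.

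**Step 2. Inputs for an illustration.**

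- Evaluable women per arm: 500 × (1 − 0.10) = 450, from the Sample size calculation section.
- Design effect: 20% versus 16%, risk ratio 0.80, from the same section.
- True risk in both arms, no drug effect: 18%. This is an assumption.
- Recording: complete in the control arm, 10% or 20% lower in the aspirin arm. These are assumptions; no such rates are in the documents.

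**Step 3. Formulas.** Observed aspirin-arm rate p_a = 0.18 × (share recorded); control rate p_c = 0.18. SE = √{[p_c(1 − p_c) + p_a(1 − p_a)]/450}; z = (p_c − p_a)/SE; two-sided rejection rate ≈ Φ(z − 1.96) + Φ(−z − 1.96). This is a plain two-proportion approximation, not the adjusted regression model planned for the analysis.

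**Step 4. Results with no true effect.**

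- 10% fewer recorded: p_a = 0.18 × 0.90 = 0.162, risk ratio 0.90. SE = √[(0.18 × 0.82 + 0.162 × 0.838)/450] = 0.0251; z = 0.018/0.0251 = 0.72; rejection about 11%.
- 20% fewer recorded: p_a = 0.18 × 0.80 = 0.144, risk ratio 0.80. SE = √[(0.18 × 0.82 + 0.144 × 0.856)/450] = 0.0245; z = 0.036/0.0245 = 1.47; rejection about 31%.

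In counts, 450 × 0.18 = 81 expected cases per arm, so these scenarios mean about 8 or 16 uncounted cases across 13 hospitals.

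**Step 5. Sensitivity to the assumed risk.** At the protocol's own control rate of 20% in both arms, 10% or 20% under-recording gives about 12% or 35%. A deficit of 5% gives about 7%. At 20% under-recording the observed rates are 20% and 16%, the very contrast the trial is designed to detect.

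**Step 6. Other patterns.**

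- If the true rates are 20% and 16% but only 80% of control cases are recorded, the observed control rate is 0.20 × 0.80 = 16%. The comparison is then 16% versus 16% and a real effect is hidden.
- If both arms under-record equally, the risk ratio and the 5% error rate are unchanged; only power falls.

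**The case against.** The strongest reply has four parts.

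*The outcome is defined by numbers.* The Primary outcome section sets thresholds and says efficacy is judged by that definition. A reader might infer from the Data collection section that the endpoint is the diagnosis the treating clinician wrote down. The text does not say so: maternity records can hold dated pressures and laboratory values, and case report forms are used as well. That objection stands, and the stronger reading should not be pressed. Nor does the article say in words that clinicians choose the urine test; this is inferred from the dipstick condition and from the use of routine records.

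*The figures do not measure the dipstick clause.* That is right. The clause matters only for women with qualifying pressures, two 2+ dipsticks, no qualifying ratio and a 24-h result that is, or would be, below 300 mg. The illustration instead supposes that a share of all aspirin-arm cases goes uncounted. It shows how sensitive the comparison is, not how large the bias will be.

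*The criteria are the adopted guideline definition.* The article presents them so, and a repeat pressure guards against misclassification from a single reading. This is fair; the definition itself is not the fault.

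*Silence in a condensed article proves little.* The schedule figure, the additional file and the full protocol are not shown and may set a common testing schedule or masked adjudication, and both arms receive the same standard antenatal care. This also stands, so the absence of a masked step is not held against the plan. What remains rests on what is printed: open allocation, and a definition in which the tests performed help to decide who is a case.

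**Conclusion.** The point holds in a limited form. Allocation is known to all, and case status depends on rechecked pressures and on the urine tests collected. Unequal work-up or classification by arm could therefore create or hide a difference in PE. That is a possibility, not a demonstrated bias: it arises only if the arms are handled differently, and neither its direction nor its size can be derived from the documents.

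The figures of about 11% and 31% depend wholly on the assumed 18% risk, 450 women per arm, no true effect, and 10% or 20% fewer recorded aspirin-arm cases. Their use is to show that modest differential recording can match the effect sought.

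A reader might also infer that the dipstick condition by itself favours aspirin. It does not: on that route, extra testing of control women would remove control cases. The change is worth making because it is cheap and keeps the design. It improves on open classification, without implying that the present definition is wrong.

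**What to change.** 1. For every woman with a reading of at least 140/90 mmHg after 20 weeks, or with a recorded PE diagnosis, enter in the eCRF the dated blood pressures and all urine protein results.
2. Derive PE and preterm PE from these values with one prespecified program that applies the definition in the Primary outcome section. Run it on a dataset without the allocation variable, and lock the result before allocation is merged.
3. Report by arm the number and type of blood pressure measurements and urine tests.
4. Keep the clinician's diagnosis as a sensitivity analysis.

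The cost is some extra data entry for the women concerned and one program, within the existing eCRF and data management. No extra assessor, visit or procedure is needed.

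The limits should be stated with the change. It removes bias in turning results into cases and lets unequal testing be seen. It cannot supply a result that was never measured, so it does not remove bias in which tests were ordered. Nor would fixing an order of precedence among the urine tests do so: wherever a quantitative test outranks dipstick, as the 24-h collection already does, an extra test can still change a woman's classification.

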#### Secondary outcomes

The secondary outcomes include maternal and neonatal outcomes, maternal serum biomarkers (including sFlt1, sEng and PlGF) and placental samples. The key secondary outcomes are shown in Table 1.

**Table 1 Tab1:** Key secondary outcomes of the APPEC study

Maternal	Preterm PE
	Severe PE
	Caesarean section delivery
	Placental abruption
	Antepartum haemorrhage
	Postpartum haemorrhage < 500 ml and < 1000 ml
Infant	Preterm birth
	Low birth weight
	Gestational age at delivery
	SGA < 10th percentile
	Intrauterine foetal death
	Stillbirth
	Neonatal intensive care unit admission
	Neonatal death
Placental and angiogenic growth factors	sFlt1
	sEng
	PlGF

*Abbreviations: APPEC* Low-dose Aspirin in the Prevention of Pre-Eclampsia in China, *PE* Pre-eclampsia, *PlGF* Placental growth factor, *sEng* Soluble endoglin, *sFlt1* Soluble fms-like tyrosine kinase 1, SGA Small for gestational age

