In most previous studies, the recommended dose of aspirin for PE prevention has been 60 to 150 mg/d, and 100 mg/d is used most commonly [13]. Studies recommend the initial use of aspirin after 12 weeks of gestation, and there is no research on aspirin treatment before 12 weeks of gestation [6]. Previous studies also have shown that the prevention of PE and foetal growth restriction using aspirin has a dose-response effect, and thus LDA is recommended to be initiated before 16 weeks of gestation [14]. Regarding drug safety, aspirin appears not to increase the rate of placental abruption, postpartum haemorrhage or foetal intracranial haemorrhage [6].

The prophylactic use of LDA for PE was first reported in 1978 [15], and since then numerous studies have reported the potential value of LDA in PE prevention among high-risk pregnant women. Authors of a Cochrane meta-analysis published in 2004 reported that the administration of antiplatelet agents in high-risk women could reduce the rate of PE by 19% [16]. The World Health Organization and several countries, including the United States, the United Kingdom, Canada and Australia, also recommended in their guidelines the use of LDA for the prevention of PE in high-risk pregnant women [17–21].

However, regarding the details of aspirin as a preventive treatment for PE, guidelines differ considerably from country to country. In addition, most randomized controlled trials (RCTs) have focused on Caucasian or black individuals; data for Asian populations are lacking [22]. Besides, only a few small-sample studies in China have been reported [23, 24]. There is scant evidence from large RCTs to guide the use of LDA for PE prevention for Chinese pregnant women. Therefore, we decided to conduct a large-population RCT in China to evaluate the role of LDA prophylactic treatment for PE prevention to fill this important gap in the literature and to ultimately translate research into practice by providing policy recommendations.

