#### Inclusion criteria

Aged ≥ 18 and < 55 yearsSingleton pregnancyLive foetus at gestational age 12–20 weeksBe at high risk of developing PE based on clinical risk factors such as the following:a. At least one high-risk factor, namely history of PE, diabetes mellitus (type 1 or 2) or chronic hypertensionb. At least two intermediate-risk factors, including obesity (≥28 kg/m^2^), advanced maternal age (≥ 35 years), family history of PE (mother and/or sister) or nulliparityFit to undergo all procedures listed in the protocolAble to provide written informed consent

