### Statistical analysis

Baseline characteristics will be calculated using Student’s *t* test, the chi-square test or Fisher’s exact test as appropriate for comparisons across groups. Data will be analysed on an intention-to-treat basis to compare primary and secondary outcomes in both groups. The primary analysis will be done with generalized estimating equation regression models of the occurrence of PE, with adjustment for the effect of the risk factors for PE at screening and the study sites. The OR with 95% CI will be calculated to quantify the treatment effect. Moreover, exploratory subgroup analysis will be performed to identify whether the effects of intervention vary with the risk factors for PE, including chronic hypertension, pre-existing diabetes, history of PE, obesity, advanced age, nulliparity and family history of PE. The initial intervention weeks of gestation (e.g., < 16 weeks vs. ≥16 weeks of gestation) and its interaction with aspirin preventive treatment will also be investigated. A *P* value < 0.05 will be considered statistically significant. Statistical analysis will be performed by a statistician using IBM SPSS Statistics version 22.0 (IBM, Armonk, NY, USA) and Stata version 11.0 (StataCorp, College Station, TX, USA) software.

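### Table 1 gives postpartum haemorrhage, a key secondary outcome, only upper limits (below 500 ml and below 1000 ml); the inequality signs are very probably reversed

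*Protocol article*

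**What the plan says.** The Secondary outcomes section of the protocol article introduces its table with "The key secondary outcomes are shown in Table 1". Among the maternal rows is "Postpartum haemorrhage < 500 ml and < 1000 ml". That is the only place in the article where postpartum haemorrhage is tied to a volume of blood loss.

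The condition is mentioned once more, in the Background, which says of drug safety that "aspirin appears not to increase the rate of placental abruption, postpartum haemorrhage or foetal intracranial haemorrhage". That sentence reports earlier literature and gives no threshold, so it neither repeats nor corrects the table.

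The Statistical analysis section plans an intention-to-treat comparison of primary and secondary outcomes. It names the odds ratio with a 95% confidence interval as the measure of treatment effect.

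**The concern.** A haemorrhage outcome is normally defined by a loss at or above some volume. Here both limits run the other way, so a woman with little bleeding satisfies the row and a woman with severe bleeding does not. The row is a stated definition of a named key outcome, so the point is not about detail left to a fuller document.

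Bleeding is an obvious maternal harm to look for with an antiplatelet drug, and the trial is meant to inform recommendations on aspirin use in China. If the row were coded as printed, a bleeding excess on aspirin could be reported as a deficit.

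**Working it through.** No planned figure is involved, so there is nothing to reproduce. The check is one of logic, followed by one illustration.

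**1. Could the sign have been lost in text conversion?** The two kinds of sign are kept apart elsewhere in the same text. The Inclusion criteria have "obesity (≥28 kg/m^2^), advanced maternal age (≥ 35 years", and the Statistical analysis section has both signs side by side: "e.g., < 16 weeks vs. ≥16 weeks of gestation". In Table 1 itself the less-than sign is used sensibly for small for gestational age. A conversion artefact is therefore unlikely. It is not fully excluded, because the PDF cannot be seen and a bare greater-than sign is not used as a comparator anywhere else in the text.

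**2. What does the row select?** Let L be the blood loss.

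- Read jointly: {L < 500} and {L < 1000} = {L < 500}. The 1000 ml limit is redundant.
- Read as two outcomes: {L < 500} lies inside {L < 1000}, and neither contains any loss of 1000 ml or more.
- Read as grades among women already diagnosed with haemorrhage: losses of 1000 ml or more still have no grade.

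| Loss | L < 500 | L < 1000 | L ≥ 500 | L ≥ 1000 |
|---|---|---|---|---|
| 300 ml | yes | yes | no | no |
| 700 ml | no | yes | yes | no |
| 1500 ml | no | no | yes | yes |

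The printed signs pick out the smallest losses. With the signs turned round, the two limits become nested severity levels. For inclusive limits, each printed condition is the exact complement of the reversed one. If strict limits were meant, the two differ only for a loss of exactly 500 ml or exactly 1000 ml.

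**3. What happens to the odds ratio?** Let p0 and p1 be the risks of a loss at or above the limit in the control and aspirin groups.

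- Intended: OR = [p1/(1 − p1)] / [p0/(1 − p0)].
- Complement: OR = [(1 − p1)/p1] / [(1 − p0)/p0] = 1 / (intended OR).

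This holds for any risks strictly between 0 and 1. The article gives no haemorrhage rates, so the following are assumptions for illustration:

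- p0 = 0.05, p1 = 0.08: intended OR = (0.08/0.92)/(0.05/0.95) = 0.08696/0.05263 = 1.65; complement = 1/1.652 = 0.605.
- Rates exchanged (p0 = 0.08, p1 = 0.05): intended OR = 0.605; complement = 1.65.
- Equal rates: both are 1.

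The strength of the effect on the odds scale is unchanged and only the direction flips.

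**The case against.** The strongest reply is that this is a visible slip that nobody would act on. The row is labelled as a haemorrhage, the two volumes look like the usual pair of cut-offs, and a coder would hardly record women without bleeding as cases. The eCRF and analysis code are not shown. Adverse events and serious adverse events are also recorded prospectively for all participants, with severity and causality (Safety monitoring), so this row is not the only route by which bleeding could be detected. All of this stands. It limits the consequence, but it does not make the printed definition usable.

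Three stronger readings are tempting, and the article does not support them.

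- **That the harm would be diluted almost to nothing.** On a risk-ratio scale the assumed rates give 0.92/0.95 = 0.968 for the complement, against 0.08/0.05 = 1.6 for the intended outcome, so a 60% relative increase seems to shrink to a 3% decrease. The effect measure that the article names is the odds ratio, and there the complement gives the exact reciprocal.
- **That losses of 1000 ml or more are lost from the trial altogether.** If the limits are two separate outcomes, the severe level can be recovered as the complement of the second. It drops out only if the limits are joined into one condition, or if they are used as grades among diagnosed cases with no further grade recorded.
- **That nearly all women will be reported as cases.** This requires both that the row label is ignored and that the printed signs were carried into data capture or code. Nothing shown establishes either.

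**Conclusion.** The point holds as an internal error in a stated outcome definition, very probably a typographical reversal of both signs. It is not a deliberate design choice.

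Taken literally, the row excludes the largest losses under every reading. Coded literally as two outcomes, it would reverse the direction of the odds ratio (1.65 against 0.605 at the assumed 5% and 8%). The reversal does not depend on those rates. It does depend on the error having reached the eCRF or the analysis code, and the article is silent on that.

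The view that a loss below 500 ml is not a haemorrhage rests on common usage, since the article does not say so. The absence of any lower limit is visible from the signs alone. The primary outcome, its analysis and the sample size are untouched. Because the row concerns a key bleeding outcome in a trial of an antiplatelet drug, it should be corrected rather than left for readers to interpret.

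**What to change.** - Restate the Table 1 row as lower limits on postpartum blood loss at 500 ml and at 1000 ml. The sponsor should confirm whether each limit is strict or inclusive, since the article does not settle this.
- State that these are two separate outcomes, the second nested in the first, each compared between groups in its own right.
- Check that the eCRF fields, their permitted ranges and the analysis code use the corrected direction. Where the measured volume is stored, derive both outcomes from it. If only categories were captured, confirm that losses at or above 1000 ml have one.

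The cost is one corrected table row and a short check of the eCRF and code. No change to recruitment, sample size or the primary analysis follows.
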